### 1.1. Objectives

#### 1.1.1. Primary Objective

To evaluate the effects of HD-tDCS on respiratory function and neurophysiological responses associated with stimulation of the diaphragmatic primary motor cortex in individuals with ALS.

#### 1.1.2. Secondary Objectives

▪To assess cortical excitability by measuring patterns of facilitation, inhibition, active and resting motor thresholds, central motor conduction time, cortical silent period, and Motor Evoked Potentials (MEPs) in individuals with ALS;▪To evaluate cortical tissue perfusion in the region of the diaphragmatic primary motor cortex in individuals with ALS through specific respiratory tests before and after the HD-tDCS intervention protocol;▪To assess respiratory muscle electrical activity in individuals with ALS before and after the HD-tDCS intervention protocol;▪To observe the effects of HD-tDCS on aspects such as respiratory muscle strength, nasal inspiratory and expiratory pressures, and peak cough flow through specific respiratory tests in individuals with ALS;▪To observe the effects of HD-tDCS on clinical and functional aspects using the Amyotrophic Lateral Sclerosis Functional Rating Scale—Revised (ALSFRS-R);▪To assess motor control and muscle performance using a protocol for evaluating peripheral muscle electrical activity;▪To assess fatigue, dyspnea, pain, sleep, quality of life, and cognition before and after the HD-tDCS intervention protocol;▪To identify adverse effects of HD-tDCS on the diaphragmatic motor cortex in individuals with ALS.

## 2. Methods

### 2.1. Study Type and Sample

This is a multicenter, parallel, controlled, randomized, triple-blind clinical trial following the criteria set by the Consolidated Standards of Reporting Trials (CONSORT) [33] and Standard Protocol Items Recommendations for Interventional Trials (SPIRIT) (Figure 1) [34]. The study will be conducted between 2025 and 2027 at three leading research centers. The purpose is to analyze the effects of HD-tDCS on the primary diaphragmatic motor cortex in subjects with a clinical diagnosis of ALS.

The study population will consist of patients clinically diagnosed with ALS by a neurologist based on diagnostic tests (clinical aspects, electrodiagnostic, genetic, and neuroimaging) [35] and the criteria established by the El Escorial World Federation of Neurology [36]. The participants will include individuals of both sexes who are being monitored in the outpatient clinics of the study centers.

### 2.2. Sample Recruitment, Randomization, and Blinding

Participants will be recruited by direct invitation to the Neuromuscular Disease Clinic of the University Hospital, where they have already been diagnosed and receive follow-up care from a multidisciplinary team. Only those who meet the eligibility criteria will be included in the study. After being invited to participate and given a clear explanation of all procedures involved in the research, including the possibility of being assigned to the control or experimental group, each individual will have one week to discuss the decision with their family. Following this period and after signing written consent, participants will be taken to the lab for baseline evaluation. Patients will receive interventions at home and will be evaluated at outpatient units and research labs. Being informed of the benefits of conducting tDCS therapy at home may enhance patient adherence to treatment by reducing transportation costs and associated risks.

The sample will consist of individuals with ALS who have signed the Informed Consent Form (ICF) (Supplementary Materials S1) authorizing their participation in the research and meet the study’s inclusion criteria. Participants will be randomized by an external researcher (using sealedenvelope.com) into two groups: the HD-tDCS group (gTDCS) and the sham group (gSham). Randomization will be carried out in a 1:1 ratio with permutation blocks of size unknown to the investigators. Each participant will have an equal probability of being assigned to either group. Evaluators, therapists, and participants will be blinded to the group allocations, as will the person responsible for statistical analysis.

The planned sample will seek a balanced distribution between the sexes whenever possible, recognizing the influence of the variations in the effects of transcranial stimulation due to the anatomy of the skull, cortical excitability, and neuroplasticity. The HD-tDCS device is configured to allow a preset stimulus model with specific timing and intensity codes, which cannot be identified during intervention. These codes, associated with each intervention group, will be programmed and provided by an external researcher to maintain blinding.

### 2.3. Eligibility Criteria

Participants will be included in the study if they meet the following inclusion criteria: individuals of both sexes with a clinical diagnosis of ALS according to the revised El Escorial criteria, aged between 18 and 80, Forced Vital Capacity (FVC) > 50% of the predicted value, sniff nasal inspiratory pressure (SNIP) > 40 cmH_2_O, and access to a telephone for contact with the support team.

Exclusion criteria include individuals who are unable to understand or complete any study steps; do not wish to participate or voluntarily withdraw at any time; have cardiac, chronic respiratory diseases or musculoskeletal comorbidities; are on invasive mechanical ventilation; have a tracheostomy; use a pacemaker, cerebral metal implants, or other electronic implants; have a cochlear implant; have epilepsy or a family history of epilepsy; have a history of stroke or tumors; have a high risk of severe hemodynamic variation, acute infectious, or inflammatory processes; are pregnant at the time of data collection; or do not complete the intervention protocol.

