## Abstract

**Background/Objectives:** Amyotrophic Lateral Sclerosis (ALS) is a progressive and fatal neurodegenerative disease characterized by motor neuron loss, muscle weakness, and respiratory dysfunction, often culminating in ventilatory failure. Evidence suggests that High-Definition Transcranial Direct Current Stimulation (HD-tDCS) may modulate motor cortical excitability and potentially influence motor and respiratory function in ALS. This study aims to evaluate the effects of home-based HD-tDCS applied over the primary diaphragmatic motor cortex on respiratory parameters and disease progression in individuals with ALS. **Methods:** This is a multicenter, randomized, controlled clinical trial. Eligible participants (aged 18–80, both sexes, diagnosed with ALS) will be randomized into an active HD-tDCS group (gTDCS) or a sham group (gSham). The intervention consists of 30 min daily HD-tDCS sessions (3 mA) applied for two weeks (5 days/week), using a 4 × 1 ring configuration targeting the diaphragmatic motor cortex. Sham stimulation includes an identical setup but only delivers ramp currents (30 s) with a minimal ongoing current (0.1 mA). **Results:** Pre-, intra-, and post-intervention evaluations will include measures of cortical excitability, cerebral and tissue perfusion, surface electromyography, respiratory and pulmonary function, fatigue, sleep quality, pain, motor performance, dyspnea, quality of life, and adverse effects. All procedures will be conducted at participants’ homes with appropriate safety monitoring. **Conclusions:** This study will investigate the effects of HD-tDCS on respiratory and motor function in ALS and explore the feasibility of a home-based neuromodulation intervention. The outcomes may provide insight into non-pharmacological strategies for respiratory management in ALS.

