#### HD-tDCS Protocol and Patient Familiarization

After being introduced to the HD-tDCS device, patients will receive explanations about the intervention protocol based on the application code for their assigned intervention group, along with instructions on their positioning and expected behavior during the application. Next, an adaptation and simulation protocol for HD-tDCS is conducted. The application area will be marked on a cap that the patient will wear during the intervention.

To accurately determine the stimulation site, individual structural Magnetic Resonance Imaging (MRI) data obtained during the first evaluation will be processed using the HD-Explore v 8.0.0 (Soterix Medical, New York, NY, USA) software for electric field modeling. This computational approach will guide the precise placement of electrodes to ensure targeted stimulation of the left primary motor cortex (M1) of the diaphragm [15]. The stimulation site will be identified as 1 cm anterior to the primary motor area, corresponding to the C3 position in the 10–20 EEG system, following established localization procedures.

The final electrode montage will be optimized using HD-Targets (Soterix Medical, New York, NY, USA), aligning with Montreal Neurological Institute (MNI) coordinates. The anode will be positioned over the diaphragmatic motor cortex region (3 mA), surrounded by four cathodes (0.75 mA) within a 75 mm radius from the central electrode, ensuring focalized current delivery. Once determined, the stimulation site will be marked on a cap worn by the patient throughout the intervention to maintain consistency across sessions.

For the HD-tDCS4x1 sessions, the 1 × 1 mini-CT Stimulator Model 1601 neurostimulator will be used, coupled with the 4x1-C3A HD-tDCS Multi-Channel adapter Explore (Soterix Medical, New York, NY, USA), which includes a kit with electrodes, plastic enclosures, conductive gel, elastic caps, and connector cables. To prevent electrode oxidation, all procedures will include careful cleaning, inspection, and the application of a consistent amount of conductive gel.

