Participants will be reassessed after 10 sessions/two weeks of intervention (T1), one month after the start of the intervention (T2), three months after the intervention (T3), and six months after the end of the interventions (T4). At each session, monitoring will be conducted to assess any side effects or adverse events, or freely through phone calls if the participant finds it necessary. Adverse events will be considered as any unfavorable medical occurrence in a participant, including any abnormal sign, symptom, or disease temporarily associated with the participant’s involvement in the research. No changes will be made to any ongoing standard clinical treatment. The intervention that the gtDCS group will receive consists of 10 tDCS sessions, 5 times per week, over two consecutive weeks, with each session lasting 32 min (Figure 2).

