Although techniques such as neuronavigation and real-time functional neuroimaging allow for more precise stimulation, their absence does not preclude the clinical application of neuromodulation. Previous studies indicate that stimulation based on standardized anatomical coordinates—even without neuronavigation—can produce physiologically relevant effects, especially when the target is the primary motor cortex, whose location is relatively well defined. However, anatomical variability among individuals, both in cortical positioning and in the functional representation of the diaphragm, may influence individual responses to the intervention. This variability underscores the importance of complementary functional monitoring, such as the use of functional neuroimaging techniques (fNIRS, EEG) or physiological measurements (respiratory pressures, electromyography), to validate the response to the protocol. Moreover, if no statistically significant differences are observed between the gSham and gTDCS groups, the findings will still yield important insights regarding the feasibility, safety, and methodological challenges of implementing HD-tDCS in individuals with ALS. These results may guide future adjustments to stimulation parameters, participant stratification strategies, or the incorporation of additional biomarkers.

Therefore, the selection of a cortical target—particularly the diaphragmatic primary motor cortex—is supported by anatomical, functional, and clinical evidence. The strategy aims to modulate cortical respiratory drive, enhance sensorimotor integration, and provide compensatory support in the face of the progressive failure of lower motor neurons—a central mechanism in the pathophysiology of ALS.

In terms of dissemination, the results of the study will be shared through peer-reviewed publications, as well as presentations at national and international conferences, particularly those focused on ALS, neurostimulation, and respiratory therapies. Additionally, we plan to make the data publicly available in open-access repositories to ensure transparency and foster further research in this field.

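### Withdrawal and non-completion are written as exclusion criteria, so the protocol as worded removes randomised participants for post-randomisation events

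*Protocol article*

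**What the plan says.** Section 2.3 (Eligibility Criteria) gives one list of exclusion criteria. Most items can be checked at screening. Two are different in kind:

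- people who "do not wish to participate or voluntarily withdraw at any time";
- people who "are pregnant at the time of data collection; or do not complete the intervention protocol".

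The refusal half of the first item and the pregnancy half of the second are not at issue. The withdrawal half and the non-completion half are.

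Section 2.2 makes the list decisive: "Only those who meet the eligibility criteria will be included in the study". It also fixes the allocation: "Randomization will be carried out in a 1:1 ratio with permutation blocks of size unknown to the investigators". Section 2.4 shows that assignment precedes treatment, because "patients will receive explanations about the intervention protocol based on the application code for their assigned intervention group", and the active course "consists of 10 tDCS sessions, 5 times per week, over two consecutive weeks". Assessments follow at T1 to T4, the last of them six months after the intervention ends.

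No section says that people excluded under these two items stay in follow-up or are analysed in their assigned arm.

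**The concern.** An exclusion criterion should be decidable before randomisation. These two are not: completion is known only at the end of the two-week course, and withdrawal without a time limit can occur up to T4.

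Removing participants on such grounds is harmful when stopping is linked both to the arm and to the outcome. Either link is plausible here. Section 2.4 gives 3 mA for 30 minutes in one arm and 0.1 mA between ramps in the other. Section 3 names discomfort, itching and redness, and provides for discontinuation when such effects persist. Section 4 says that progression varies widely between patients, so people who stop because they are deteriorating would differ in prognosis from those who finish.

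The rule also cuts across what the trial hopes to learn. Identifying adverse effects is a secondary objective (Section 1.1.2). The Abstract says the study will "explore the feasibility of a home-based neuromodulation intervention". Section 4 says that after a null result "the findings will still yield important insights regarding the feasibility, safety, and methodological challenges". If people who stop early are taken out of the study, non-completion and intolerance may be understated in just those results.

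**Working it through.** **1. Timing.** Section 2.2 randomises, Section 2.4 then delivers ten sessions under the assigned code, and Section 2.3 excludes those who do not finish. The third step depends on the second, so the exclusion must act on people already randomised. For withdrawal, only the part of the period before randomisation is a legitimate screening matter.

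**2. Figures in the document.** Section 4 gives 3 × 20 = 60 participants, hence 30 per arm at 1:1, with power 0.80 and significance level 0.05. It gives no effect size, SD or drop-out rate. There is no stated figure for this point to reproduce, and everything below rests on assumed inputs.

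**3. Bias of a completers-only difference.** Let p_A and p_S be the proportions not completing in the active and sham arms, and m the amount, in SD, by which non-completers would have scored worse.

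- If m is measured against completers, completers exceed their arm's full mean by m·p, so the bias is m(p_A − p_S).
- If m is measured against the whole-arm mean, the shift is m·p/(1 − p), so the bias is m[p_A/(1 − p_A) − p_S/(1 − p_S)].

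| p_A, p_S | m | against completers | against whole-arm mean |
|---|---|---|---|
| 20%, 10% | 0.8 | 0.16 − 0.08 = 0.08 | 0.200 − 0.089 = 0.11 |
| 20%, 10% | 0.5 | 0.10 − 0.05 = 0.05 | 0.125 − 0.056 = 0.07 |
| 30%, 10% | 1.0 | 0.30 − 0.10 = 0.20 | 0.429 − 0.111 = 0.32 |
| 5%, 3% | 0.8 | 0.040 − 0.024 = 0.02 | 0.042 − 0.025 = 0.02 |

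All are in SD and favour active. If m differs between arms, the first formula becomes m_A·p_A − m_S·p_S, so equal drop-out rates do not by themselves guarantee zero bias. With m = 0 the bias is zero whatever the rates.

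**4. A second model, as a cross-check.** Suppose there is no treatment effect, only the active arm loses a fraction d, and being excluded correlates ρ with poor outcome. The bias is ρ·φ(z_d)/(1 − d). For d = 20% and ρ = 0.5 this is 0.5 × 0.280/0.80 = 0.175 SD. The standard error is √(1/24 + 1/30) = 0.274, and a two-sided 5% test would reject in about 10% of trials. For d = 10% and 30% at the same ρ, the bias is 0.10 and 0.25 SD and rejection about 7% and 14%. Loss from one arm only is deliberately unfavourable.

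**5. Precision.** The difference detectable with 80% power (t-test, two-sided 5%) is 0.74 SD at 30 per arm, 0.78 at 27 and 0.83 at 24, that is, after losing 10% or 20%.

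**The case against.** The strongest reply is that these are reasons for discontinuation put under the wrong heading, and that the article has no analysis section. Analysis sets are commonly left to a statistical analysis plan, which is not shown. This stands in part. A reader might infer that the plan states a completers-only analysis. It does not; that comparison is what the wording permits if applied. But the point does not rest on a missing analysis set. Section 2.3 states a rule, and a later document naming all randomised participants would contradict it.

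A reader might also infer that safety data are lost and that completion is 100% by construction. The text does not support that. Adverse events are monitored at each session (Section 2.4), all participants in both arms are questioned (Section 2.6.8), and a participant with persisting effects is monitored until they resolve (Section 3). The commitment to CONSORT (Section 2.1) and the flow diagram in Figure 1 give a place to count non-completers. Feasibility is not among the objectives in Section 1.1. The risk is understatement, not loss.

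On size, nothing in the article supports 20% or 30% non-completion. The course is short, at home and given by trained staff, and Section 2.6.8 expects few adverse effects. The 5% and 3% row is a fair lower case. Section 4 says the sample-size calculation will allow for dropouts, so the loss of precision may already be covered. That allowance addresses numbers; it does not address bias.

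**Conclusion.** The point holds on the wording. Two events that can occur after randomisation are exclusion criteria, inclusion is tied to those criteria, and no other section reverses the effect. The reasoning in step 1 needs no assumption.

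The size does. On the central assumed inputs the bias is about 0.08 SD towards active, or 0.11 SD if non-completers are compared with the whole-arm mean. It becomes negligible with low, similar drop-out and vanishes if stopping is unrelated to outcome. If more sham than active participants stopped, it would run the other way. These figures show what is at risk and do not predict it. The precision figures carry little weight here.

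The wording should be corrected before anyone is removed under it, because follow-up that was never collected cannot be recovered.

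**What to change.** - Delete voluntary withdrawal and non-completion of the intervention from the exclusion criteria in Section 2.3. Apply the item on being unable to understand or complete study steps at screening only.
- Record two separate events: stopping stimulation, and withdrawing consent to follow-up.
- Continue T1 to T4 assessments for those who stop stimulation and still consent. For those who withdraw consent, keep the data collected up to that point.
- State that the main analysis includes all randomised participants in their assigned arm, with completers as a sensitivity analysis.
- Report adverse effects in everyone who had at least one session, and completion by arm.

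The cost is a change of wording and a few more follow-up visits. The estimate may be slightly diluted compared with one in completers. Participants who withdraw consent will still have missing data, which this change does not remove.

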### 2.4. Interventions

Participants in the gTDCS will receive anodal high-definition direct current stimulation at an intensity of 3 mA on the diaphragmatic motor cortex through electrodes fixed in a cap. The stimulation will begin with a 30 s ramp-up to reach the intended intensity, followed by a 30 min session, and ending with a 30 s ramp-down. This will be conducted daily for 2 weeks (10 days), excluding weekends, at the same time each day in the participant’s home. The anodal current was chosen for motor cortex stimulation due to its potential for functional modulation, without directly inducing action potentials or neuronal hyperexcitability [25]. The intervention will be administered by a trained research professional with experience in neuromodulation techniques.

In the gSham, individuals will undergo all steps of the intervention and assessment protocol, but stimulation will be set to reach an intensity of 0.1 mA after the initial 30 s ramp-up, with the 3 mA current only returning in the last 30 s, resulting in no significant intervention during the 30 min.

#### HD-tDCS Protocol and Patient Familiarization

After being introduced to the HD-tDCS device, patients will receive explanations about the intervention protocol based on the application code for their assigned intervention group, along with instructions on their positioning and expected behavior during the application. Next, an adaptation and simulation protocol for HD-tDCS is conducted. The application area will be marked on a cap that the patient will wear during the intervention.

To accurately determine the stimulation site, individual structural Magnetic Resonance Imaging (MRI) data obtained during the first evaluation will be processed using the HD-Explore v 8.0.0 (Soterix Medical, New York, NY, USA) software for electric field modeling. This computational approach will guide the precise placement of electrodes to ensure targeted stimulation of the left primary motor cortex (M1) of the diaphragm [15]. The stimulation site will be identified as 1 cm anterior to the primary motor area, corresponding to the C3 position in the 10–20 EEG system, following established localization procedures.

The final electrode montage will be optimized using HD-Targets (Soterix Medical, New York, NY, USA), aligning with Montreal Neurological Institute (MNI) coordinates. The anode will be positioned over the diaphragmatic motor cortex region (3 mA), surrounded by four cathodes (0.75 mA) within a 75 mm radius from the central electrode, ensuring focalized current delivery. Once determined, the stimulation site will be marked on a cap worn by the patient throughout the intervention to maintain consistency across sessions.

For the HD-tDCS4x1 sessions, the 1 × 1 mini-CT Stimulator Model 1601 neurostimulator will be used, coupled with the 4x1-C3A HD-tDCS Multi-Channel adapter Explore (Soterix Medical, New York, NY, USA), which includes a kit with electrodes, plastic enclosures, conductive gel, elastic caps, and connector cables. To prevent electrode oxidation, all procedures will include careful cleaning, inspection, and the application of a consistent amount of conductive gel.

Participants will be reassessed after 10 sessions/two weeks of intervention (T1), one month after the start of the intervention (T2), three months after the intervention (T3), and six months after the end of the interventions (T4). At each session, monitoring will be conducted to assess any side effects or adverse events, or freely through phone calls if the participant finds it necessary. Adverse events will be considered as any unfavorable medical occurrence in a participant, including any abnormal sign, symptom, or disease temporarily associated with the participant’s involvement in the research. No changes will be made to any ongoing standard clinical treatment. The intervention that the gtDCS group will receive consists of 10 tDCS sessions, 5 times per week, over two consecutive weeks, with each session lasting 32 min (Figure 2).

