In terms of survival, the lack of curative treatments or those that significantly alter the clinical course and progression of ALS has led to the search for new treatment alternatives, proposed in recent years. Over the last two decades, new therapeutic hypotheses have emerged, based on case studies on the application of transcranial direct current stimulation (tDCS). Specifically, different forms of modulation based on non-invasive brain stimulation techniques have been tested and evaluated as non-pharmacological methods for treating various neurological conditions.

tDCS is a brain modulation technique with a strong physiological basis and significant practical acceptance in the treatment of various neurological and musculoskeletal disorders. Studies point to interesting possibilities for using tDCS in treating motor and sensory dysfunctions and learning disorders, making it a potential adjunct to conventional treatments [12,13]. Stimulation can last minutes or even hours after the end of the session. Thus, it emerges as a potential tool for treating motor neuron diseases and degenerative neurological syndromes. Given its ease of application, minimal adverse effects, and relatively low cost, tDCS is clearly a feasible option for routine use in public and supplementary healthcare systems [17,18].

Although widely used, conventional tDCS has evolved into a more advanced form known as high-definition tDCS (HD-tDCS) [19]. This modality features smaller electrodes and a configuration involving a central electrode, with either anodic or cathodic current, surrounded by two or more electrodes with opposite polarity [20,21,22,23]. This configuration helps confine neuromodulation effects to the radius of the four electrodes and increases the focal effect, producing better results in the different areas of the stimulated motor cortex, including the diaphragmatic cortex, to investigate, for instance, changes in muscle strength and perceived exertion [23].

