#### 2.5.4. Cortical Excitability—Transcranial Magnetic Stimulation (TMS)

Cortical excitability will be assessed using a Neuro-MS TMS device (Neurosoft Ltd., Ivanovo, Russia). MEPs will be recorded via surface electromyography (sEMG) from the hemidiaphragms, with activity captured using a NEURO-MEP amplifier (Neurosoft Ltd., Russia) with a 5 Hz low-pass filter and a 50 mV acquisition range. Stimulation will be non-invasively and painlessly administered with a Neuro-MS device connected to an “8”-shaped coil placed over the diaphragmatic motor cortex in the left hemisphere. The vertex and interaural and nasion–inion lines will be marked on a cap based on the 10/20 system, with a 1 × 1 cm grid drawn as a TMS reference [50,51].

The left primary motor cortex “hotspot” will be identified as the scalp location eliciting MEPs ≥ 50 μV in the respiratory muscles in at least 5 of 10 stimulations at the end of expiration, and during inspiration, respectively. For all TMS pulses, the “8”-shaped coil connected to a magnetic stimulator will initially target the primary diaphragmatic motor cortex, approximately 3 cm to the left of the midline and 2–3 cm anterior to the auricular plane [15,51]. The coil will be held by the operator and angled at 45° to the midline, with the handle pointing posteriorly, generating a posterior–anterior current flow in the brain during monophasic pulse delivery [52].

Surface EMG electrodes will be positioned bilaterally on the 7th and 8th intercostal spaces to monitor diaphragmatic motor responses [53,54]. TMS will be delivered at 80% of the maximum magnetic output at end-expiration, with participants in the sitting at 45° position. Diaphragmatic EMG will be continuously monitored to guide coil orientation, which will be adjusted around the stimulation hotspot to elicit the largest Motor Evoked Potentials (MEPs) during inspiration. Stimulation will be repeated five times at 45–60 s intervals, with the three highest-quality traces selected for analysis.

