The cortical target will be identified and marked on the cap as the first grid location and explored in adjacent directions until optimal responses are obtained. To ensure accurate and consistent segmentation, the assessment will be processed using HD-Explore software (Soterix Medical, New York, NY, USA) for electric field modeling. The MRI image will be uploaded to the platform server, and the resulting individual model will be automatically integrated into the software for personalized anatomical mapping. Individual anatomical MRI scans will retrospectively confirm that stimulation was applied over the diaphragmatic motor cortex, located near the midline of the precentral gyrus, approximately 3 cm lateral to the vertex, as first described by Maskill et al. [51] and later investigated in studies on diaphragmatic corticospinal excitability in COPD and COVID-19 [15,55,56,57] (Figure 6). While absolute anatomical certainty is not achievable without combined TMS-fMRI, this protocol employs advanced neuronavigational procedures to maximize targeting accuracy.

After localization, the following will be evaluated: latency, amplitude, resting motor threshold (rMT), active motor threshold (aMT), corticospinal excitability, and cortical silent period (CSP). MEPs will be expressed as a percentage of average amplitude and analyzed for latency and area. Intracortical inhibition (SICI, LICI at 2 ms) and intracortical facilitation (SICF at 15 ms) will be assessed using 10 pulses (minimum 7) at 90% aMT [58,59,60].

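### The HD-tDCS site for the left diaphragmatic motor cortex is tied to C3, but Section 2.5.4 places the same cortex about 3 cm from the midline, and nothing says which location governs the anode

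*Protocol article*

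**What the plan says.** The subsection HD-tDCS Protocol and Patient Familiarization (under Section 2.4) names the target as the left primary motor cortex of the diaphragm. It gives three statements about where the anode goes:

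- Individual structural MRI is processed for electric-field modelling: "This computational approach will guide the precise placement of electrodes".
- The site will be identified as "1 cm anterior to the primary motor area, corresponding to the C3 position" of the 10–20 system.
- "The final electrode montage will be optimized using HD-Targets", in alignment with MNI coordinates. The anode is then placed over the diaphragmatic motor cortex region, with four cathodes "within a 75 mm radius from the central electrode". The site is marked on a cap that is used for all sessions.

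Section 2.5.4 locates the same cortex in the same hemisphere twice. The TMS coil starts "approximately 3 cm to the left of the midline" and 2–3 cm in front of the auricular plane. The cortex itself is "located near the midline of the precentral gyrus, approximately 3 cm lateral to the vertex". The caption of Figure 6 also references the diaphragmatic motor cortex from Cz, not C3.

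On navigation, Section 2.5.4 says that "this protocol employs advanced neuronavigational procedures to maximize targeting accuracy", while Section 5 refers to the absence of neuronavigation technologies.

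**The concern.** C3 is the only explicit scalp landmark given for the anode, and it does not agree with the location that Section 2.5.4 gives for the target. The protocol does not rank the landmark against the modelled montage, so staff at three centres could read the instruction differently. Because the site is marked once on the cap and reused, an error in one participant would persist through all ten sessions.

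The stake is interpretation. Section 1.1.1 ties the primary objective to stimulation of the diaphragmatic primary motor cortex, and the Introduction argues that the 4 × 1 ring "helps confine neuromodulation effects to the radius of the four electrodes". If the anode stood several centimetres from the target, an observed effect could not confidently be credited to that cortex. A null result could not confidently be read as evidence that stimulating it does nothing.

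**Working it through.** The protocol gives no distance for C3, so there is no stated figure to reproduce. The check is whether C3 can be the same place as a point about 3 cm from the midline.

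**Inputs**
- Target: about 3 cm left of the midline, or lateral to the vertex (Section 2.5.4).
- Limit on cathode distance: 75 mm from the central electrode (HD-tDCS Protocol and Patient Familiarization).
- Assumption, not in the documents: C3 lies 20% of the ear-to-ear arc lateral to the vertex.
- Assumption, not in the documents: an adult ear-to-ear arc of 30–40 cm.

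Section 2.5.4 uses a 1 × 1 cm grid drawn on a cap, so distances are taken along the scalp.

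**Lateral gap** = 0.20 × arc − 3 cm

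| Arc (cm) | C3 lateral to vertex (cm) | Gap to 3 cm (cm) |
|---|---|---|
| 30 | 0.20 × 30 = 6.0 | 3.0 |
| 36 | 0.20 × 36 = 7.2 | 4.2 |
| 40 | 0.20 × 40 = 8.0 | 5.0 |

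**Sensitivity**
- Arc at which C3 would be 3 cm out: 3 / 0.20 = 15 cm, which is half the low end of the assumed range and not an adult head.
- If the approximate 3 cm is stretched to 4 cm: 6.0 − 4 = 2.0 cm to 8.0 − 4 = 4.0 cm.
- Straight-line lateral distance on a sphere with radius R = arc/π, so that C3 sits 36° from the vertex: R·sin 36° − R·sin(3/R) = 2.7 cm (arc 30), 3.8 cm (arc 36) and 4.5 cm (arc 40).
- The C3 phrase can describe the stimulation site, or the motor area from which the site is 1 cm forward. The 1 cm shift runs front to back, so the lateral gap is the same on both readings. Any front-to-back offset can only add to the total distance.

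**Against the ring**
- 3.0 / 7.5 = 40% and 5.0 / 7.5 = 67% of the 75 mm limit.
- With cathodes at the limit, the target is off-centre but still inside the ring. It falls outside only if the actual radius is smaller than the gap, and the protocol states an upper limit, not the radius used.

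**The case against.** The strongest reply is that C3 never decides anything. The subsection opens with individual MRI and modelling to determine the site, ends with an optimised final montage, puts the anode over the diaphragmatic motor cortex region, and marks the cap only once the site is settled. On that sequence C3 is at most a starting landmark and the fault is one of wording. This is a fair reading and may well be the intended one. It does not dispose of the point: the C3 sentence is phrased as how the site will be identified, it is not called provisional, and nothing says that the model prevails over it.

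It is also true that the 3–5 cm rests on two outside assumptions. They are declared, and the direction survives every plausible value.

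Two stronger readings are tempting, and the documents do not support them.

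- A reader might infer that Sections 4 and 5, which defend standardized anatomical coordinates, flatly contradict the individual placement described earlier. But the montage sentence itself invokes MNI coordinates, so the intervention text already combines individual modelling with a standardized frame. The caveat in Section 5 concerns the functional representation of the diaphragm, which a structural MRI does not measure. That section opens with TMS coil positioning, so the caveat may partly concern TMS. The sentence on coordinates in Section 4 reports previous studies.
- A reader might infer that using standardized coordinates would itself displace the anode by 3–5 cm. Sections 4 and 5 never mention C3. The coordinates in Section 2.5.4 would give no lateral gap, and the gap with MNI coordinates cannot be computed because no coordinate is given. Only literal use of C3 produces 3–5 cm.

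The clash over neuronavigation may be terminology: MRI-based modelling in one place, tracked navigation in the other.

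**Conclusion.** The point holds in a conditional form. The protocol gives two incompatible lateral locations for one target, and literal use of C3 would place the anode about 3–5 cm lateral to the location in Section 2.5.4 (2–4 cm if the stated distance is read as 4 cm). If the modelled montage overrides C3 in every participant, the anode may be correctly placed and only the text is wrong. The documents do not show which applies, so they do not support a claim that participants will be stimulated at the wrong site.

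The active-versus-sham comparison stays valid either way. The exposure is limited to attributing an effect or a null result to the diaphragmatic motor cortex. It should be corrected because the error sits in the placement instruction itself and costs almost nothing to remove. Confidence is medium, since the size depends on the assumed C3 position and head size, and the practical effect depends on a precedence rule that the text omits.

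**What to change.** In HD-tDCS Protocol and Patient Familiarization, delete the equivalence with C3. State that the individual MRI-modelled diaphragmatic M1 site, expected about 3 cm lateral to the vertex, sets the anode position and overrides any scalp landmark.

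As a minor point, make Section 2.5.4 and Section 5 agree on whether neuronavigation is used and what the term means.

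The cost is wording only: MRI, field modelling, montage optimisation and cap marking are already planned. Recruitment was scheduled to start on 31 July 2025, so the anode site actually used should be documented for anyone treated before the correction. Recording the distance from the anode to the TMS hotspot, where one is found, would be a useful description but is optional. It would be an added measurement and should not set the placement.
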